# 1. SUMMARY OF THE STUDY

| **Title** | Lymphocytic enteritis with negative coeliac serology and clinical and histological response to a gluten-free diet: double-blind randomized clinical trial with rechallenge of gluten vs. placebo. | |
| --- | --- | --- |
| **Study code** | EL-DSG/07/2011 | |
| **Objectives** | To demonstrate hypersensitivity to gluten in patients with lymphocytic enteritis, and clinical response and histology of a gluten-free diet despite the presence of IgA negative tissue anti-transglutaminase antibodies. | |
| **Treatment** | Sachets with gluten (10 g) or placebo (maltodextrin: 10 g): 1 sachet every 12 hours. | |
| **Study design** | Prospective, randomized, double-blind, placebo-controlled, with parallel groups of gluten rechallenge vs. placebo, for 24 weeks, in patients following a gluten-free diet.   - Group A: Powdered gluten (10 g every 12 hours) - Group B: Placebo (10 g every 12 hours)   Determination of digestive clinical state, adherence to diet, coeliac serology, histology, flow cytometry, and tissue anti-transglutaminase antibodies in intestinal mucus membrane, at baseline and after gluten rechallenge or placebo (whether clinical digestive symptoms reappear at 4 or 12 weeks, or at the conclusion of the study at 24 weeks). | |
| **Study population** | Inclusion criteria:  1. Signed informed consent  2. Age 18 or older  3. Confirmed histological diagnosis of lymphocytic enteropathy (LE)  5. Coeliac-positive genetic study (HLA-DQ2 and/or HLA-DQ8)  6. Negative coeliac serology  7. Complete clinical and histological response to gluten-free diet  8. Initial clinical signs with or without extra-intestinal manifestations | |
|  | Exclusion criteria:  1. Inability to adhere to the scheduled visits or other protocol requirements, in the judgement of the investigator  2. Participation in a clinical trial in the previous 30 days, simultaneous participation in a trial, or prior participation in the present study  3. History of gluten-sensitive enteropathy with villous atrophy or positive serology  4. Lymphocytic enteropathy or initial response to gluten-free diet but following a normal diet at the time of selection | |
| **Sample size** | 20 patients | |
| **Length of treatment** | 24 weeks | |
| **Primary efficacy variables** | Reappearance of clinical digestive signs and histological recurrence | |
| **Secondary efficacy variables** | - Clinical signs at 4 weeks - Clinical signs at 12 weeks - Flow cytometry to measure percentage of lymphocytes CD3+ gamma-delta+ and CD3- in intestinal mucus membrane | - Assessment of IgA tissue anti-transglutaminase antibodies in the intestinal mucus membrane - IgA tissue anti-transglutaminase antibodies in serum and anti-endomysium antibodies |

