**8. DEVELOPMENT OF TRIAL AND ASSESSMENT OF RESPONSE**

**8.1. PRINCIPAL AND SECONDARY ASSESSMENT VARIABLES**

**Efficacy criteria**

- Primary efficacy evaluation variable: Reappearance of clinical digestive signs (24 weeks)
- In addition, secondary efficacy variables will be evaluated:
  - Clinical signs at 4 weeks
  - Clinical signs at 12 weeks
  - Flow cytometry to measure percentage of lymphocytes CD3+ gamma-delta+ and CD3- in intestinal mucus membrane
  - Assessment of IgA tissue anti-transglutaminase antibodies in the intestinal mucus membrane
  - IgA tissue anti-transglutaminase antibodies in serum and anti-endomysium antibodies
  - Quality of life according to the GIQLI questionnaire.
  - Histological changes on biopsy in the distal duodenum

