**8.2. DEVELOPMENT OF TRIAL, NUMBER OF VISITS, COMPLEMENTARY EXPLORATIONS**

The subjects will be selected according to the inclusion and exclusion criteria established in this protocol. In the event of a patient fulfilling the inclusion criteria and none of the exclusion criteria, he or she will be informed of the existence of the study, of its characteristics, and of the advantages and disadvantages in participating in it. Patients will be given an information sheet and their consent to participate in the study will be requested.

Those patients agreeing to take part in the study will receive a numerical code with which they will randomly receive one or the other of the medical treatment types.

After the start-up, the subject will be seen at 1, 3, and 6 months, as stipulated, and more frequently if necessary.

In the pre-inclusion visits, comprehensive bloodwork, coeliac serology, coeliac genetic study (HLA-DQ2/HLA-DQ8, if not already done), and distal duodenal biopsy, for pathological anatomy and flow cytometry, will be carried out.

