**8.3. DESCRIPTION OF METHODS USED TO ASSESS RESPONSE**

Clinical response will be measured with analogue visual scales ranging from 0 to 100, administered at baseline and at each visit up to 6 months, for symptoms of abdominal pain, abdominal swelling, diarrhea, and flatulence (total score 0 to 400 points) (Appendix 6).

Patient quality of life will be evaluated in the first visit and the last (at 6 months, or at early withdrawal) using the GIQLI questionnaire (Gastrointestinal Quality of Life Index), which has been shown to yield valid, reliable scores for the detection of significant clinical changes in the lives of patients regarding their health (Eypasch E et al. Gastrointestinal Quality of Life Index: development, validation and application of a new instrument. Br J Surg 1995; 82:216-22; Quintana JM et al. Translation and validation of the Gastrointestinal Quality of Life Index (GIQLI). Rev Esp Enferm Dig 2001; 93:693-706) (See Appendix 3).

At the first visit and the last (or at early withdrawal from the study) a distal duodenal biopsy will be drawn for histological study, and evaluation of tTG deposits and lymphocytic sub-populations (using flow cytometry) will be made.

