**8.4. WITHDRAWAL CRITERIA**

Any patient may withdraw from the study at any time without incurring any personal penalty and without the need for explanation. Withdrawal must be noted in the CRF when it occurs, along with the results to date and the reason(s) for withdrawal, if given.

The investigator may also withdraw a patient from the study upon consideration of the risks and benefits thereof, and determination that the former outweigh the latter with continued participation. The CRF must reflect the date and main cause for the withdrawal, as well as any further observations that may be made at the time of withdrawal. Among the reasons for withdrawing a patient early from the study are the following (the main reason should be indicated):

• Lack of efficacy of treatment, e.g.:

– Progression of the illness under study in comparison to baseline.

(in the six weeks following).

– The need to administer a concomitant medication that is prohibited in the treatment of the illness under study.

• Intolerable adverse events.

• Lack of patient cooperation, e.g.:

– Patient request.

– Lack of therapeutic compliance or failure to carry out visits according to the agreed calendar.

– Technical or logistical reasons (e.g., change of patient residence).

– Pregnancy or breast-feeding, either existing or planned.

• Others (must be noted), e.g.:

– Diagnosis different from that of the study.

All patients withdrawing early from the study must be seen within 7 days of the last administration of the medicine used in the study. This final visit is to be duly recorded in the CRF.

The investigator will continue to observe all patients withdrawing early from the study as a result of intolerable adverse events until the findings have been resolved.

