**13. STATISTICAL ANALYSIS**

The calculation for the sample size is based on the main variable of efficacy—that is, the rate of recidivism at 6 months. On the basis of results of previous studies it was determined that the rate of recidivism with the reintroduction of gluten would be 80%, and with placebo 20%. Assuming a 10% patient drop-out rate, an alpha value of 5%, and statistical power (beta) of 80%, for a bilateral test it was calculated that 10 patients would be needed for each patient group (bearing in mind that analyzing the results would require a Chi-square test with Yates correction). The total number, then, is 20 patients.

Excluded from this analysis are those subjects presenting significant departures from the protocol.

All of the evaluations of the primary and secondary variables, both of efficacy and of safety, are understood in the exploratory sense (alpha=0.05, bilateral).

The Chi-square test with Yates correction will be used for independent groups and the Fisher exact test for qualitative variables. For intergroup comparison of the quantitative variables, the Student-t test will be used for parametric variables, and the Mann-Whitney U-test for non-parametric variables.

The finding of values for differences of p less than 0.05 will be considered significant. The rates for clinical remission between treatment groups will be expressed proportionally with the corresponding bilateral interval of confidence of 95%, as an estimation of therapeutic effect.

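### If assessment ends when symptoms return, the week-12 symptom comparison omits week-4 relapsers, and final biopsy and serology follow shorter exposure on gluten than on placebo

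*Protocol*

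**What the plan says.** The study design row of the Summary (section 1) schedules clinical state, serology, histology, flow cytometry and mucosal antibodies at baseline and again after rechallenge. It ties the second occasion to "whether clinical digestive symptoms reappear at 4 or 12 weeks, or at the conclusion of the study at 24 weeks". Section 8.3 adds: "At the first visit and the last (or at early withdrawal from the study) a distal duodenal biopsy will be drawn for histological study". No other post-baseline biopsy is provided for.

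Section 8.4 gives "Progression of the illness under study in comparison to baseline" as an example of a reason for early withdrawal. Patients who withdraw early "must be seen within 7 days of the last administration of the medicine used in the study", and no later efficacy visit is described.

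Other passages point to full follow-up. The Summary gives the length of treatment as 24 weeks. Section 8.2 says that "the subject will be seen at 1, 3, and 6 months, as stipulated, and more frequently if necessary", and the symptom scales in section 8.3 are "administered at baseline and at each visit up to 6 months". Section 8.4 says only that the investigator may withdraw a patient.

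Section 8.1 lists "Clinical signs at 12 weeks" as a secondary variable, with histology, cytometry and antibodies at no stated exposure time. The Summary also names histological recurrence as primary. Section 13 compares the arms with ordinary two-group tests and assumes that "the rate of recidivism with the reintroduction of gluten would be 80%, and with placebo 20" (per cent), at 6 months.

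**The concern.** If the final assessment takes place when symptoms return, the outcome sets how long each patient is observed, and the protocol expects that outcome four times as often on gluten (80% / 20% = 4).

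This has two consequences. A patient whose last visit was at week 4 has no week-12 score. The week-12 comparison then leaves out the earliest relapsers, most of them on gluten, and tends to understate the difference between arms. Secondly, the biopsy and antibody results come after shorter exposure on gluten than on placebo. A normal biopsy after 4 weeks of gluten is weaker evidence than one after 24 weeks. This matters because section 4.1 looks to the histological response and the mucosal immunology after reintroduction to settle whether these patients have coeliac disease.

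**Working it through.** The protocol states no figure for exposure at biopsy or for week-12 signs, so there is none to reproduce.

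**Inputs from the protocol.** Relapse by 6 months R = 0.80 on gluten and 0.20 on placebo (section 13); 10 patients per arm (section 6.3); visits at 1, 3 and 6 months (section 8.2), taken as weeks 4, 12 and 24 as in the Summary.

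**Assumptions.** Assessment ends at the visit where relapse is found. The protocol gives no timing of relapse, so several are tried. Other drop-out is ignored.

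**Formulas.** Let a, b and c be the shares of relapses found at weeks 4, 12 and 24, with a + b + c = 1.

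- Mean weeks to final biopsy = R(4a + 12b + 24c) + 24(1 − R)
- Still assessed at week 12, of 10 = 10(1 − aR)
- Signs at week 12 among those = bR / (1 − aR)
- Cumulative relapse by week 12 = R(a + b)

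**Equal spread (a = b = c = 1/3).**

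- Exposure, gluten: 0.8 × 40/3 + 0.2 × 24 = 10.67 + 4.80 = 15.5 weeks
- Exposure, placebo: 0.2 × 40/3 + 0.8 × 24 = 2.67 + 19.20 = 21.9 weeks
- Week-12 signs among those remaining: 0.267/0.733 = 36% v 0.067/0.933 = 7%
- Cumulative relapse: 0.8 × 2/3 = 53% v 0.2 × 2/3 = 13%

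**All at week 4 (a = 1).**

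- Exposure: 0.8 × 4 + 0.2 × 24 = 8.0 v 0.2 × 4 + 0.8 × 24 = 20.0 weeks
- Remaining at week 12: 2 v 8 patients, none with signs, although 80% v 20% have relapsed

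All timings, gluten v placebo:

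| Assumed timing of relapse | Weeks to final biopsy | Still assessed at week 12, of 10 | Signs among those | Cumulative relapse by week 12 |
|---|---|---|---|---|
| All at week 4 | 8.0 v 20.0 | 2.0 v 8.0 | 0% v 0% | 80% v 20% |
| Half at 4, half at 12 | 11.2 v 20.8 | 6.0 v 9.0 | 67% v 11% | 80% v 20% |
| Equal over 4, 12, 24 | 15.5 v 21.9 | 7.3 v 9.3 | 36% v 7% | 53% v 13% |
| Constant hazard | 15.5 v 22.4 | 7.6 v 9.6 | 42% v 7% | 55% v 11% |
| All at week 12 | 14.4 v 21.6 | 10 v 10 | 80% v 20% | 80% v 20% |

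Apart from the last row, the difference among those remaining is smaller than the cumulative difference: 29 points instead of 40 under equal spread, for example. Excluding the last row for week 12 only, gluten exposure runs from 40% (8.0/20.0) to 71% (15.5/21.9) of placebo exposure across the table. Both imbalances vanish only if every relapse is found at week 24.

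**Direction.** If the shares a and b are the same in both arms, the difference among those remaining is 0.6b / (1 − a + 0.16a²), against 0.6(a + b) cumulatively. The cumulative difference is larger because (a + b)(1 − a + 0.16a²) − b = a(1 − a − b) + 0.16a²(a + b), which is positive whenever a > 0. If the timing differs between arms, the direction is not guaranteed. With all placebo relapses at week 4 and all gluten relapses at week 12, those remaining show 80% v 0%, against 80% v 20% cumulatively.

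**The case against.** The strongest reply is that no sentence ends the challenge at relapse. The Summary gives 24 weeks of treatment, the symptom scales run to 6 months, and withdrawal for progression is at the investigator's discretion. A reader might infer from the Summary that patients must leave when symptoms return; the documents do not say so. This stands, and it is why the point is conditional. It does not remove the problem, because one biopsy timed by symptom return and also placed at the last visit is hard to fit with anything except a last visit at relapse.

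A second reply is that how a week-4 relapser counts at week 12 belongs in a statistical analysis plan, and that section 6.3 already sets intention to treat. A plan not shown here may settle the binary case. But intention to treat does not create a week-12 score for someone who has left, and no analysis plan can supply a biopsy at a common exposure time.

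A third reply is that taking the biopsy when symptoms return is a deliberate choice, and that section 8.3 already makes histology an end-of-exposure result. This is fair. A positive biopsy at relapse remains informative, and the protocol nowhere says that a negative one in an early relapser counts against a coeliac-type response. What is missing is any acknowledgement that exposure differs by arm.

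Finally, section 13 calls all evaluations exploratory, and week-4 signs and relapse by 24 weeks are untouched. This stands and limits the severity.

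**Conclusion.** The point holds conditionally, with moderate severity. The Summary and sections 8.3 and 8.4 need reconciling in any case. If assessment ends at relapse, the week-12 symptom comparison omits week-4 relapsers and, with similar relapse timing in both arms, is biased towards no difference. The size depends on timing that the protocol does not give: 36% v 7% instead of 53% v 13% under equal spread, 0% v 0% instead of 80% v 20% at one extreme, and no bias if all relapses are found at week 12. Mean exposure at the final biopsy and serology is 8.0 v 20.0 weeks with all relapses at week 4, and 15.5 v 21.9 under equal spread, so a negative result in an early relapser is less informative.

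Three stronger readings are tempting. A reader might infer that the week-12 comparison covers only patients who tolerated the sachets; it does not, because those who relapse between weeks 4 and 12 are still seen at week 12. A reader might expect a week-12 difference of zero; that needs every relapse to fall at week 4, and the week-4 comparison would then show the whole effect. A reader might think the main result is compromised; relapse by 24 weeks is naturally cumulative and is not affected. Histology carries more weight only because the Summary calls its recurrence primary, while section 8.1 lists histology as secondary.

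**What to change.** 1. Reconcile the Summary with sections 8.3 and 8.4, so that the protocol states whether assessment continues after symptoms return. Which rule applies is for the investigators to say.
2. In section 8.1 and the Summary, define the symptom variables as relapse by week 4, by week 12 and by week 24 in all randomised patients, with a relapsed patient counted as relapsed at every later time point. This works however item 1 is settled.
3. Report histology, flow cytometry and antibody results with weeks of exposure by arm, and note short exposure as a limit on negative results.

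Two further steps are best avoided. Carrying the exit symptom score forward to later visits adds an assumption that the relapse definition does not need. Reading negative histology or serology only in patients who completed 24 weeks selects on the outcome again: at 80% v 20%, about 2 gluten and 8 placebo patients would be left.

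The cost is wording, with no added visit, biopsy or patient. Cumulative relapse gives up information on how severe symptoms are at week 12, and a patient whose symptoms later subside still counts as relapsed. Unequal exposure at biopsy is disclosed, not removed.

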**6. SUBJECT SELECTION**

**6.1. INCLUSION CRITERIA**

1. Signed informed consent

2. Age 18 or older

3. Confirmed histological diagnosis of lymphocytic enteropathy (LE)*

5. Coeliac-positive genetic study (HLA-DQ2 and/or HLA-DQ8)

6. Negative coeliac serology

7. Complete clinical and histological response to gluten-free diet

8. Initial clinical signs with or without extra-intestinal manifestations

*Lymphocytic enteropathy is defined as an intraepithelial lymphocyte count greater than 25 per 100 epithelial cells, using histochemical techniques with anti-CD3 monoclonal antibodies for the count.

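### Histology is a yes/no primary event in the Summary but a secondary change measure in section 8.1; comparing arms on the lymphocyte count would avoid cut-off misclassification and use the biopsies better

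*Protocol*

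**What the plan says.** The Summary lists as primary efficacy variables "Reappearance of clinical digestive signs and histological recurrence". Section 8.1 names clinical digestive signs at 24 weeks as the one primary variable and places duodenal biopsy changes among the secondary ones.

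The only numerical histological criterion is a footnote to the diagnostic inclusion criterion in section 6.1: "Lymphocytic enteropathy is defined as an intraepithelial lymphocyte count greater than 25 per 100 epithelial cells". Entry also requires "Complete clinical and histological response to gluten-free diet", with no count attached. Recurrence has no count attached either.

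Section 8.3 provides paired material: "At the first visit and the last (or at early withdrawal from the study) a distal duodenal biopsy will be drawn for histological study". Section 13 sizes the trial on a recidivism rate at 6 months, without saying whether this is clinical, histological or both. It compares proportions by Yates chi-square or Fisher, and quantitative variables by Student t or Mann-Whitney.

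**The concern.** Two things are at stake.

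1. **Status and form of the histological endpoint.** In one place histology is part of the primary outcome and is an event. In the other it is secondary and is a change. The two call for different analyses.

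2. **How an event would be read.** If the diagnostic cut-off is reused, a patient moving from 24 to 26 is a recurrence and one moving from 8 to 24 is not. Patients sitting just under 25 on the diet can then change category with no change in the mucosa. Such misclassification falls on both arms and narrows the difference between them. With 20 patients, one or two chance crossings per arm matter. Section 4.1 wants the clinical and histological response to gluten, together with mucosal immunology, to support a definitive diagnosis.

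**Working it through.** **The plan's own figure.** Inputs from section 13: 80% v 20%, "an alpha value of 5%, and statistical power (beta) of 80%, for a bilateral test", "Assuming a 10% patient drop-out rate", and "analyzing the results would require a Chi-square test with Yates correction".

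- Uncorrected: n = [1.96·√(2·0.5·0.5) + 0.842·√(0.8·0.2 + 0.2·0.8)]² / 0.6² = (1.386 + 0.476)² / 0.36 = 9.6, so 10 per arm.
- With continuity correction: (9.63/4)·[1 + √(1 + 4/(9.63·0.6))]² = 12.7, so 13 per arm. With 10% dropout, 13/0.9 = 14.4, so 15.

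The stated 10 matches only the uncorrected figure without dropout. That is a separate matter. It is noted here because it leaves little room for dilution: exact Yates power at 80/20 with 10 per arm is 63.5%.

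**Chance crossing of 25, true density unchanged.** The simplest model is Poisson counting alone, P(reading > 25 per 100):

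| True IEL per 100 | 100 cells | 300 cells | 500 cells |
|---|---|---|---|
| 15 | 0.6% | 0% | 0% |
| 18 | 4.5% | 0.3% | 0.02% |
| 20 | 11% | 2.6% | 0.7% |
| 22 | 22% | 12% | 7% |
| 24 | 37% | 33% | 30% |

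A fuller model makes these assumptions, none of them from the protocol: true IEL is normal with SD 3 between patients; between-biopsy CV is 0–25%; 100–500 cells are counted; the baseline reading is 25 or less. Each reading is Poisson(true × lognormal factor × N/100) × 100/N. Share crossing with no gluten effect:

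- mean 10: at most 0.8%; mean 12: at most 1.9%; mean 14: at most 4%;
- mean 18: 1.9–7.1% at CV 0, and 5.6–12.6% at CV 15–25%;
- mean 20: about 5–19% over the whole range.

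Selecting on a low baseline reading adds a small upward drift: 0.08 to 1.6 IEL at mean 18, under 0.6 at mean 14.

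**What misclassification costs.** If a fraction f of non-recurrences is misread as recurrence in both arms, p becomes p + (1 − p)f. Suppose section 13's rates refer to histology and f = 10%. Then 0.8 + 0.2·0.1 = 0.82 and 0.2 + 0.8·0.1 = 0.28. Exact Yates power at 10 per arm falls from 63.5% to 51%. At f = 5% it is 57%.

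**Crossing v count.** Assume 80% of the gluten arm rise by 15 IEL, none on placebo do, mean IEL is 18, and there are 10 per arm (3,000 simulated trials per setting):

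| Analysis | CV 15%, 100 cells | CV 25%, 300 cells |
|---|---|---|
| Fisher on crossing 25 | 0.62 | 0.53 |
| Mann-Whitney on change | 0.80 | 0.74 |
| Final count adjusted for baseline | 0.87 | 0.82 |

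Repeat runs differ by one to three points and keep the order. In the first setting about 81% of true risers are read above 25 and about 9.6% of the others are. Crossing rates are therefore 0.8·0.81 + 0.2·0.096 = 67% on gluten against 9.6% on placebo, not 80% against 0%. With mean 14 included, crossing has about 52–62% power and the adjusted count about 83–91%. The gain therefore does not depend on chance crossings being common. These figures compare analyses; they do not estimate the power of this trial.

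**The case against.** A reader might infer that recurrence can only be judged at 25, that entry and event thresholds coincide, and that noise alone produces recurrences in both arms. The protocol supports none of these as fact. The cut-off belongs to the diagnosis. A complete response could mean normalisation well below 25, and an SAP or pathology procedure could define recurrence. Chance crossings are close to nil if on-diet counts are low.

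The effect on the primary endpoint is also limited. Under section 8.1 histology is not primary. If the Summary's conjunction requires both components, a noisy count cannot create a primary event alone: with 10% noise independent of symptoms and section 13's 20% placebo rate, false composite events are about 0.10 × 0.20 = 2%.

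Section 8.1 already speaks of changes, section 13 has tests for quantitative variables, and section 7.4 keeps the evaluator blind. Nothing prescribes reducing the secondary variable to crossed or not crossed. Section 13 also calls all evaluations exploratory.

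All of this stands and limits the point. What it leaves is the conflict over the status of histology, and the Summary's choice of a yes/no event where a count is available.

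**Conclusion.** The point holds in a limited form. The Summary and section 8.1 disagree on whether histology is primary and on whether it is an event or a change. If the event is read on the only stated cut-off, chance crossings of about 0–4% at mean IEL 14 or below, 2–13% at mean 18 and 5–19% at mean 20 are to be expected in either arm. They are non-differential, so they cost power without favouring gluten.

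The firmer argument is efficiency. With the assumed rise of 15 IEL in 80% of the gluten arm, the baseline-adjusted count has about 83–91% power against about 52–62% for crossing. At mean 18, a rank test on change, already available under section 13, reaches about 74–80%. On-diet mean, SD, CV, cells counted and size of rise are all assumptions. This is a worthwhile and cheap improvement, not a flaw that invalidates the design.

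**What to change.** - Reconcile the Summary with section 8.1 on whether histology is primary, and say whether the Summary requires both components.
- State that the between-arm histological comparison is made on the IEL count per 100 epithelial cells at the final biopsy, taking account of the patient's own baseline count. A baseline-adjusted model would be an addition to section 13; Mann-Whitney on the change would not.
- Have both slides of each patient counted blind, on the same fixed number of epithelial cells.
- Report crossing 25 descriptively only, beside the change from baseline.

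A minimum rise added to the cut-off, such as 10 per 100, is not recommended. The value is arbitrary. In the same simulations it lowers power from 0.62 to 0.58 and from 0.53 to 0.49, and it lowers the share of true recurrences labelled from about 81% to 72%, although it cuts false ones from about 10% to 5%.

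Cost: wording in the protocol or SAP, slightly more counting, and a result less directly expressed as a recurrence rate. No further biopsy is needed.

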**4.2. OBJECTIVES**

To demonstrate hypersensitivity to gluten in patients with lymphocytic enteropathy and a clinical and histological response to a gluten-free diet in spite of presenting IgA negative tissue anti-transglutaminase antibodies.

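### The primary endpoint is symptoms plus histology in the Summary but symptoms alone in Section 8.1, and Section 13 calls it exploratory although the trial sets out to demonstrate an effect

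*Protocol*

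**What the plan says.** **Summary (Section 1).** The row for primary efficacy variables, in the plural, reads "Reappearance of clinical digestive signs and histological recurrence". The Summary's list of secondary variables does not include histology.

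**Section 8.1.** One primary variable is named: "Primary efficacy evaluation variable: Reappearance of clinical digestive signs (24 weeks". The secondary list ends with "Histological changes on biopsy in the distal duodenum".

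**Section 13.** The sample size rests on a single main variable, "the rate of recidivism at 6 months", assumed to be 80% with gluten and 20% with placebo. The section does not say whether this is clinical, histological or both. The effect estimate carries another label: "The rates for clinical remission between treatment groups will be expressed proportionally". On status, the section states: "All of the evaluations of the primary and secondary variables, both of efficacy and of safety, are understood in the exploratory sense". It nevertheless sets a two-sided alpha of 0.05 and treats any p below 0.05 as significant.

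**Section 4.2.** The objective is worded as confirmatory: "To demonstrate hypersensitivity to gluten in patients with lymphocytic enteropathy".

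**The concern.** Histology changes rank between the two lists. It is primary in the Summary and absent from the Summary's secondary list, but secondary in Section 8.1. So the Summary row is not simply shorthand for 8.1. The word *and* in that row can also be read in two ways: each patient must show both events (a composite), or two endpoints are tested (co-primaries). That makes three candidate primary analyses.

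They answer different questions. The justification in Section 4.1 separates coeliac disease from non-coeliac gluten sensitivity, and it looks to the clinical and histological response together with mucosal immunology. Relapse of symptoms alone does not mean the same as relapse with histological recurrence. Section 8.3 plans a biopsy at the first and last visit, and at early withdrawal, so data for every version will exist. Whoever analyses the trial could report whichever version came out better.

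The exploratory label adds a second uncertainty. The trial has a power calculation, a main variable and an aim to demonstrate, yet the protocol does not treat its primary test as confirmatory. A reader cannot tell which result would meet the objective.

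**Working it through.** **1. The plan's own figure.** Inputs from Section 13: 80% versus 20%, two-sided alpha 0.05, power 80%, 10% dropout, chi-square with Yates correction. The usual two-proportion formula without correction is

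n = [1.960·√(2·0.5·0.5) + 0.842·√(0.16 + 0.16)]² / 0.6² = (1.386 + 0.476)² / 0.36 ≈ 9.6, so 10 per group.

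This matches the stated 10 per group, but without the Yates correction or the dropout allowance that Section 13 says were included. With the correction the formula gives 13 per group, and 13/0.9 = 14.4, so 15 after dropout. That mismatch is a separate matter. What counts here is that the calculation covers one binary variable, so it supports neither two co-primaries nor a composite with other rates.

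**2. Exact power at 10 per group.** All 2×2 tables were enumerated with the Yates-corrected test. Fisher's test rejects exactly the same tables at this size.

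| Reading of the primary endpoint | Rates, gluten vs placebo | Power |
|---|---|---|
| One endpoint | 80% vs 20% (Section 13) | 63.5% |
| Two co-primaries, both must succeed, independent | 80% vs 20% each | 0.635 × 0.635 = 40% |
| Two co-primaries that always agree (upper limit) | 80% vs 20% each | 63.5% |
| Per-patient composite | 60% vs 20% (assumed) | 25% |
| Per-patient composite | 50% vs 10% (assumed) | 30% |
| Per-patient composite | 60% vs 10% (assumed) | 47% |
| Per-patient composite | 60% vs 5% (assumed) | 63% |
| Per-patient composite | 64% vs 4% (assumed; 0.8 × 0.8 and 0.2 × 0.2) | 74% |

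The protocol gives no histology rates, so every composite row is an illustration and the rows do not bound the possible range. A composite that requires both events cannot occur more often than symptoms alone in either arm. Power may still rise or fall, depending on which arm loses more events.

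**3. Type I error.** Under the null hypothesis, the same enumeration gives the test a true size of 0.76% at a common rate of 20% and a maximum of 1.28% at a common rate of 50%. If success on either of two independent binary endpoints counted, the error would be at most 1 − (1 − 0.0128)² = 2.5%.

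**4. The labels compared.**

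| Place | Term for the main outcome | Histology |
|---|---|---|
| Summary | clinical signs and histological recurrence | primary |
| 8.1 | clinical signs, 24 weeks | secondary |
| 13, sample size | recidivism, 6 months | not stated |
| 13, effect estimate | clinical remission | not mentioned |

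**The case against.** The best defence is that the operative text is not neutral. Section 8.1 is the section that defines the variables. Section 13 speaks of one main variable at 6 months and estimates the effect on clinical remission. Read together they point to symptoms alone, which leaves one row of the Summary as the outlier. This stands as far as it goes, and it makes 8.1 the natural default. It does not settle the matter, because recidivism is never defined and no text ranks 8.1 above the Summary.

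It is also fair to say that *exploratory* does not undo a randomised, double-blind comparison with a stated alpha and a sample size based on power. That stands too. The label conflicts with the objective and weakens the claim, but it does not make a positive result worthless.

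Three stronger readings are tempting, and the documents do not support them.

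- **Inflated false-positive risk.** A reader might take two endpoints at 0.05 each to give 1 − 0.95² = 9.75%, or the eight variables of Section 8.1 to give 1 − 0.95⁸ = 34%. The first ignores how conservative the planned test is at this size. The second also assumes independence among variables that include clinical signs at 4, 12 and 24 weeks in the same patients.
- **A certain loss of power under a composite.** The illustrative rates give results on both sides of 63.5%.
- **Histology as a requirement.** Section 4.1 says that these assessments would allow a definitive diagnosis. It does not say that histology is indispensable, and the objective in 4.2 is hypersensitivity.

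**Conclusion.** The contradiction is in the current text and needs correction. The primary endpoint is stated in two incompatible ways, the sample-size variable is tied explicitly to neither, and the status of the primary test conflicts with the objective. The identity of the primary endpoint belongs in the protocol, so a statistical analysis plan could not repair this without overriding one section.

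The consequence is the possibility of choosing the endpoint after the fact, and doubt over what a result would show. Power depends on the reading. The single-endpoint and co-primary figures rest on the 80% and 20% of Section 13, with the co-primary figures assuming that both endpoints share those rates. The composite figures rest on assumed rates, and even the direction of the change from 63.5% is undetermined. The type I error figure of about 2.5% applies to two independent binary endpoints under the Yates or Fisher test with 10 per group. It does not extend to the quantitative secondary variables.

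A reader might also infer that more than 25 intraepithelial lymphocytes per 100 epithelial cells defines histological recurrence. Section 6.1 gives that cut-off only as the entry definition of lymphocytic enteropathy.

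**What to change.** Before unblinding:

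1. State one primary definition in the same words in the Summary, Section 8.1 and Section 13. Clinical relapse by 24 weeks, as in 8.1, is most consistent with Section 13. A composite, or co-primaries with a stated decision rule, would also resolve the conflict if the power calculation is redone for it.
2. Define recidivism in Section 13 to match, and use the same term for the effect estimate in place of clinical remission.
3. If the 8.1 version is kept, list histology as secondary in both places.
4. Declare the primary test confirmatory at two-sided 0.05, and limit *exploratory* to the secondary and safety variables.

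With the 8.1 version the cost is wording in three places. No visit or procedure is added, since the biopsies are already planned. The sponsor gives up the freedom to choose the endpoint later. A composite or co-primary choice would need assumed histology rates and might change the sample size. If the change counts as substantial, Section 12.1 requires submission to the ethics committee.
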